### Randomisation

Figure 1 shows randomisation and progress through the trial. The doctor or midwife who performs the ultrasound will enrol eligible women. Randomisation will be completed at the antenatal clinic at GW 41^+0^ to 41^+1^. Block randomisation with a fix block size (unknown to the investigator) will be done online, 1:1, using the Pregnancy Register with a module specifically developed for the study by MedSciNet AB, Stockholm, Sweden. Stratification will be performed for centre and parity (primiparity and multiparity).

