## Methods/Design

This multicentre registry based randomised controlled trial named SWEPIS (SWEdish Post-term Induction Study), will be performed at 4 university clinics and 1 county hospital in Sweden from 01-09-2015 to 31-08-2018. The centres comprise more than 65 000 deliveries per year. Eligible participants are healthy women ≥18 years old, who are able to understand oral and written information, with a normal live singleton pregnancy in cephalic presentation at 41^+0^ GW, estimated with a first or second trimester ultrasound. Women will be excluded if they have had a previous caesarean section or other uterine surgery, pregestational and insulin dependent gestational diabetes, hypertensive disorders in pregnancy including preeclampsia, multiple pregnancy, foetus in breech or transverse position, oligohydramniosis (amniotic fluid index <50 mm or deepest vertical pocket <20 mm), small for gestational age (<−22 % according to a Swedish reference [39], foetal malformations and contraindications to vaginal delivery such as placenta previa.

The Regional Ethics Board in Gothenburg approved the study in May 2014 (Dnr: 285–14).

General information of the study will be available at each antenatal care unit where women who most likely chose to give birth at any of the including hospitals will attend. All pregnant women are given oral and written information about the study at around GW 40 at the antenatal care units. All potentially eligible women will be consecutively contacted for further information. Women who are interested in participating in the study are booked for a visit at the antenatal clinic at the respective hospital at GW 41^+0^–41^+1^. Further information is given and written informed consent is obtained. Thereafter, an ultrasound examination is performed. Women with a foetus with an estimated foetal weight <22 % according to the Swedish gestational and gender adjusted reference curve and/or AFI <50 mm or DVP <20 mm will not be randomised but will be followed-up according to clinical routine. Consenting eligible women will be enrolled and randomised. Eligible women who do not want to participate in the study will be asked to fill in a web based or postal written consent for collection of information on demographic background variables, previous postterm pregnancy and obstetric and neonatal outcomes (this is to make it possible to check for selection bias).

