### Labour induction

Women in the intervention group (early induction) will be induced within 24 h after randomisation. Women in the control (expectant management/late induction) will be induced at GW 42^+0^ (and no later than GW 42^+1^). After randomisation, women in the control group are followed-up at the ordinary antenatal clinic according to clinical routine for GW 41^+^–42^+0^.

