The primary statistical analysis will be the comparison of primary composite outcome (stillbirth, neonatal mortality and morbidity) between the two randomised groups with two-sided Fisher’s exact test on the intention to treat (ITT) [46] populations at significance level 0.05. Adjustments for baseline variables if necessary and interaction analyses will be performed with multivariable logistic regression analyses. For variables with interactions *p* <0.10 with primary efficacy variable, subgroup analyses will be performed. Women with spontaneous labour or prelabour rupture of the membranes (PROM) after randomisation but before planned induction will be included in the statistical analysis according to ITT. Women with pregnancy complications after randomisation indicating any need of intervention are included in the statistical analysis according to ITT. Foetuses/newborns with lethal birth defects will be excluded in the analysis of stillbirth, neonatal mortality and morbidity. The median, 95 % CI, quartiles, means and SD are calculated when appropriate. The Mann–Whitney U test is used to compare differences between the two groups concerning continuous variables, Fisher’s exact test for dichotomous variables, Mantel-Haenszel Chi-square test for ordered categorical variables and Chi-square test for unordered categorical variables.

The statistician will be blinded to group and intervention. Otherwise blinding is not possible for practical reasons.

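### One fixed block size in an open-label trial leaves an avoidable risk that staff who track allocations can foresee the end of each block

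*Protocol article*

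**What the plan says.** The Randomisation section of the protocol article sets 1:1 allocation and says that "Block randomisation with a fix block size (unknown to the investigator) will be done online". It adds: "Stratification will be performed for centre and parity (primiparity and multiparity". Under Methods/Design the trial "will be performed at 4 university clinics and 1 county hospital in Sweden", which gives five centres and ten strata.

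The same section assigns enrolment: "The doctor or midwife who performs the ultrasound will enrol eligible women". That ultrasound also settles eligibility. Methods/Design gives the order: "Further information is given and written informed consent is obtained. Thereafter, an ultrasound examination is performed". A woman whose scan shows low estimated foetal weight or little amniotic fluid "will not be randomised but will be followed-up according to clinical routine".

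On blinding, the Statistical analysis section keeps the statistician blinded and then says: "Otherwise blinding is not possible for practical reasons". Under Labour induction, women in the early arm "will be induced within 24 h after randomisation", so the arm is soon evident to those caring for the woman.

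**The concern.** In an open trial, concealment of the next allocation is the main protection against selective entry. The online module stops anyone from reading the list. It does not stop anyone from predicting the list from past allocations. When every block in a stratum has the same length and past allocations can be seen, the length can be worked out. Staff who know it, and who have kept count, know the remaining allocations of a block once one arm has used up its share.

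The person placed to use that knowledge measures foetal weight and amniotic fluid, and those measurements decide whether a consented woman is randomised. If measurements near a limit were read differently according to the expected arm, the groups would differ in risk at entry. Intention-to-treat analysis and a blinded statistician cannot undo that. The protocol's check for selection bias follows eligible women who decline to take part. It does not cover women who consented and were then ruled out at the scan.

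**Working it through.** The plan gives no block size and no figure for predictability, so there is nothing to reproduce. The sample size is not in dispute and serves only as a multiplier.

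**Inputs from the protocol article.** 10 038 women, 5 019 per arm, and event rates of 2.74 % and 1.84 % (Statistical analysis); five centres (Methods/Design); two parity levels (Randomisation). **Assumed:** block sizes of 4 to 20.

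**Is there enough history to infer a constant size?** 5 × 2 = 10 strata, and 10 038 / 10 ≈ 1 004 women per stratum on average. Real strata will be unequal. That is about 251 blocks of 4, or 100 blocks of 10, in an average stratum, which is ample.

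**Share of allocations that are certain.** In a block of 2m with m per arm, the expected length of the final same-arm run is 2m/(m+1). The certain share is therefore [2m/(m+1)] / 2m = 1/(m+1). Check for blocks of 4: the six orderings have final runs of 2, 1, 1, 1, 1 and 2, with mean 8/6 = 1.33, and 1.33/4 = 33 %.

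**Share guessed correctly.** A guesser who always names the arm with more places left is right in {m + [2^(2m)/C(2m,m) − 1]/2} / 2m of cases. For blocks of 4: {2 + [16/6 − 1]/2}/4 = 71 %. Chance is 50 %.

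| Assumed size | Certain share | Upper bound, of 10 038 | Correct guesses |
|---|---|---|---|
| 4 | 33 % | 3 346 | 71 % |
| 6 | 25 % | 2 510 | 68 % |
| 8 | 20 % | 2 008 | 67 % |
| 10 | 17 % | 1 673 | 65 % |
| 20 | 9 % | 913 | 62 % |

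All rows assume that the size has been inferred and that the complete, ordered sequence of the stratum is known. They are upper bounds.

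**Effect of varying the size.** Blocks drawn at random from 4, 6 and 8 were simulated over 100 000 allocations, against a guesser who knows the set of sizes and tracks everything. About 2 % of allocations are certain, and about 68 % of guesses are right. Certainty nearly disappears; educated guessing hardly changes.

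**How much steering would the planned effect need?** The planned difference is (0.0274 − 0.0184) × 5 019 ≈ 45 events. Assume that steered women have a 10 % event risk. Removing k of them from an arm at 2.74 % to reach 1.84 % requires 45.17 / (0.10 − 0.0184) ≈ 554 women. If average-risk women take their places, it requires 45.17 / (0.10 − 0.0274) ≈ 622. That is 11 to 12 % of the arm. At an assumed risk of 20 % it is still 45.17 / (0.20 − 0.0184) ≈ 249. For comparison, 50 women at 10 % risk replaced by average-risk women would shift 50 × 0.0726 ≈ 3.6 events, about 8 % of the planned difference.

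**The case against.** The protocol withholds the block size and allocates online. Anyone who wants to foresee an allocation needs the full ordered record for one centre and parity group, whoever enrolled each woman. The protocol nowhere says that enrolling staff have such a record, and in large units many operators are plausible. The room for steering is also small. Randomisation must be completed at 41+0 to 41+1 weeks, so a woman can hardly be held back for a later place. Consent comes before the scan, and exclusion rests on numeric limits. Steering would mostly mean misrecording a measurement.

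All of this stands, and it limits the size of the risk. It does not remove it: centre and parity are known to staff, the arm becomes evident locally, and the operator takes the measurements.

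Two stronger readings are tempting, and the protocol supports neither. A reader might take about 1 700 to 3 300 (sizes 10 to 4) as the number of predictable women. Those are ceilings for assumed sizes under complete tracking. A reader might also infer that a little steering could create or hide the planned one-third reduction. On the assumed 10 % risk it would take some 550 to 620 women in one arm. Half of the ceilings for sizes 4 and 10 gives about 1 673 and 836 certain places in that arm, so a third or more of them would have to be misused.

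**Conclusion.** The point holds as a cheap improvement to the design; it is not an error or contradiction in the plan. A single fixed block size within centre and parity, combined with open treatment and an enroller who decides ultrasound eligibility, leaves an avoidable risk of selection bias. Keeping the size from investigators lowers that risk without closing it. Nothing in the protocol shows that steering has occurred or is likely.

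If the size is inferred and the stratum is fully tracked, between 9 % (blocks of 20) and 33 % (blocks of 4) of allocations are certain in advance. The true ceiling depends on a size that the protocol does not give, and practical predictability should be lower. The sample size is unaffected.

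**What to change.** In the Randomisation section, replace the fixed block size with block sizes that vary at random within each centre-by-parity stratum. Mask from sites both the sizes in use and the set from which they are drawn. The Trial status section gives 01/09/2015 as the start of recruitment, so in strata already open the change should begin with the next block.

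The gain should be stated modestly. With assumed sizes 4, 6 and 8, certain allocations fall from 33, 25 or 20 % (fixed 4, 6 or 8) to about 2 %. Best-guess accuracy stays near 68 %, against 71, 68 or 67 %.

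The cost is a small reprogramming of the study's online module and slightly more possible imbalance where a stratum ends in mid-block. That imbalance is at most half the largest block, so four women per stratum if the largest size is 8. No extra women are needed.

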**Fig. 1 Fig1:**
[figure not shown]
Flow-shart of the study

### Labour induction

Women in the intervention group (early induction) will be induced within 24 h after randomisation. Women in the control (expectant management/late induction) will be induced at GW 42^+0^ (and no later than GW 42^+1^). After randomisation, women in the control group are followed-up at the ordinary antenatal clinic according to clinical routine for GW 41^+^–42^+0^.

### Methods of labour induction (early at GW 41^+0^–41^+2^ or late at GW 42^+0^–42^+1^)

Before labour induction the following examinations are performed: blood pressure, urine analysis, abdominal and cervical examination and CTG. If there are no contraindications for induction of labour, induction will be performed according to the following:if the foetal head is well engaged and the cervix is ripe (Bishop score ≥6 for primiparous and ≥5 for multiparous) amniotomy is performed. Oxytocin infusion will be started after 2 h if no or not regular contractions.if the cervix is unripe (Bishop score <6) or the fetal head is not engaged any of the following methods are used (according to the routine at the clinic):mechanical dilation using a Foley like catheter (BARD or Cook)misoprostol (Cytotec®) orallymisoprostol (Misodel®) controlled-released vaginal insertprostaglandin E2 (Minprostin®) gel vaginallyprostaglandin E2 (Propess®) vaginal insert

Mechanical dilation may be followed by prostaglandins and vice versa. If the woman is not in active labour or cervix is still unripe after 48 h, the clinician together with the woman will decide whether to perform a caesarean section or to continue expectant management until GW 42^+0^. All inductions will be performed with the patient staying at the hospital until delivery. The clinic’s protocol and guidelines for induction and surveillance during induction will be followed. During the active phase of labour fetal surveillance with continuous CTG with or without ST segment analysis (STAN) in combination with foetal scalp blood sampling is recommended.

## Outcome measures

### Primary outcome measure

A composite of stillbirth, neonatal mortality and neonatal morbidity. Stillbirth is defined as intrauterine foetal death of a foetus that was alive at randomisation. Neonatal mortality is defined as live births with death day 0–27. Neonatal morbidity is defined as at least one of the following variables: Apgar score <7 at 5 min, metabolic acidosis defined as pH <7.05 and base deficit >12 mmol/l in umbilical artery or pH <7.00 in umbilical artery, HIE I-III, intracranial haemorrhage, neonatal convulsions, meconium aspiration syndrome (MAS), mechanical ventilation, obstetric brachial plexus injury.

### Secondary outcome measures- neonates

Admittance to neonatal intensive care unit, birth weight, macrosomia (>4.5 kg), Apgar score <4 at 5 min, therapeutic hypothermia, neonatal jaundice, pneumonia, sepsis, costs.

### Secondary outcome measures-mothers

Use of epidural analgesia, caesarean section, assisted vaginal delivery, duration of labour, episiotomy, perineal lacerations III-IV, shoulder dystocia, postpartum hemorrhage (>1000 ml), chorioamnionitis, wound infection, urinary tract infection, endometritis, sepsis, costs.

Data on women’s attitudes, experiences and health-related quality of life will be collected, only in the Region Vastra Götaland subpopulation, by questionnaires (web based or postal).

#### After randomisation

Personality (Big Five), Depression/anxiety (HADS), Health related quality of life (Euro-Qol –VAS & Euro-Qol-5D, Self-efficacy (The General Self-Efficacy Scale (GES) [40–44].

Health-related quality of life (Euro-Qol –VAS & Euro-Qol-5D, the General Self-Efficacy Scale (GES),

#### Three months after delivery

Depression/anxiety (Hospital anxiety and depression scale, HADS) [44], The Childbirth Experience Questionnaire (CEQ) [41]. The instruments will be eligible in English, Spanish, Arabic, Bosnian, Croatian, Serbian, Farsi and Somali language.

For centres with the same medical record system e.g.Siemens Obstetrix (Siemens Medical solutions) we will register data on satisfaction with delivery (Visual analog scale 0–10) [45].

### Data collection

Data on background variables, obstetric and neonatal outcomes will be obtained from the Swedish Pregnancy Register and Swedish Neonatal Quality Register (SNQ) after delivery. The Pregnancy Registry is a certified national quality registry initiated by the Swedish Health care that collect and process information all the way from early pregnancy to a few months after birth. SNQ is a certified national quality registry initiated by the Swedish Health care that collect and process information about the neonate (www.snq.se).

### Statistical analysis

We anticipate that induction of labour at GW 41 as compared to induction at GW 42 will reduce the primary outcome by one third from 2.74 to 1.84 % (level of significance 0.05, power 80 %, dropout rate 10 %). The primary composite outcome of 2.74 % is based on the following rates of perinatal mortality and neonatal morbidity in GW 41^+3^ from Region Skane between 2000 and 2010: HIE 0.22 %, MAS 0.36 %, obstetric brachial plexus injury 0.05 %, Apgar score <7 at 5 min 1.58 %, stillbirth and neonatal mortality 0.53 %. We need a sample size of 10 038 women to be randomised, 5 019 to induction of labour at GW 41^+0^ and 5 019 to expectant management. Since primary outcome is a serious and rare event, we consider that a 33 % reduction is clinically relevant. In 2013, Region of Vastra Gotaland, Region Skane, Stockholm and Uppsala had 18 261, 14 719, 28 335 and 3 787 deliveries, respectively, altogether 65 102 deliveries. During a 3 year period we calculate with 195 306 deliveries. Given a rate of 18 % of women being undelivered at 41^+0^ GW, this will give us 34 755 women during 3 years. We estimate that around 33 % (11 469) of these women can be included.

The primary statistical analysis will be the comparison of primary composite outcome (stillbirth, neonatal mortality and morbidity) between the two randomised groups with two-sided Fisher’s exact test on the intention to treat (ITT) [46] populations at significance level 0.05. Adjustments for baseline variables if necessary and interaction analyses will be performed with multivariable logistic regression analyses. For variables with interactions *p* <0.10 with primary efficacy variable, subgroup analyses will be performed. Women with spontaneous labour or prelabour rupture of the membranes (PROM) after randomisation but before planned induction will be included in the statistical analysis according to ITT. Women with pregnancy complications after randomisation indicating any need of intervention are included in the statistical analysis according to ITT. Foetuses/newborns with lethal birth defects will be excluded in the analysis of stillbirth, neonatal mortality and morbidity. The median, 95 % CI, quartiles, means and SD are calculated when appropriate. The Mann–Whitney U test is used to compare differences between the two groups concerning continuous variables, Fisher’s exact test for dichotomous variables, Mantel-Haenszel Chi-square test for ordered categorical variables and Chi-square test for unordered categorical variables.

The statistician will be blinded to group and intervention. Otherwise blinding is not possible for practical reasons.

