### Complications in postterm pregnancies

Perinatal mortality (PNM) is defined as the prevalence of stillbirth (after GW 22^+0^) and neonatal mortality within 7 days after birth. The PNM in Sweden between 2004 and 2013 was 0.3‰ in GW 39–41 and 0.7‰ after 42 GW. A Danish national register study (*n* = 125 043 pregnancies) showed that PNM increased in women with postterm pregnancies as compared to women with term pregnancies (adjusted odds ratio (aOR) 1.36; 95 % CI 1.08–1.72) [8]. A Swedish register study of deliveries between 1982 and 1991 (*n* = 914 702 pregnancies) found significantly higher rates of stillbirth in primiparous women in GW 41 (1.86‰) and GW 42 (2.26‰) as compared to GW 40 (1.23‰) [4]. However, in multiparous women the risk of stillbirth was not significantly different in GW 41 (0.50‰) and 42 (0.86‰) as compared to GW 40 (0.53‰). These figures were calculated based on the number of women delivered in each GW. A recalculation with the number of non-delivered women in each GW (foetuses at risk) as denominator, showed significantly higher incidences of stillbirth in GW 41 and 42, as compared to GW 40, in primiparous women (0.62, 1.26 and 2.27‰, respectively), as well as in multiparous women (0.73, 1.00 and 1.51‰, respectively). Risk factors for stillbirth in postterm pregnancies are maternal age and obesity [11].

The risk of perinatal complications such as meconium aspiration syndrome (MAS), umbilical cord complications, asphyxia, pneumonia, sepsis, convulsions, shoulder dystocia, traumatic injuries and peripheral nerve damage is higher in postterm deliveries than in deliveries at term (aOR 1.1–2.0) [8]. A case-control study from Australia showed a higher risk of neonatal encephalopathy in children born postterm, (GW 41: aOR 3.3 and GW 42: aOR 13.2 versus GW 39) [12]. A Swedish study (*n* = 354 children) found an increased risk for developmental delay at the age of 4–4.5 years in children born postterm compared with children born at term [13]. Recently, also increased rates of obesity and early markers of the metabolic syndrome were found in children born postterm [14, 15]. This may not be a result of prolonged pregnancy per se but rather associated with foetal and/or parental genetic factors that also are associated with delayed parturition.

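### The 0.53 % stillbirth and neonatal mortality used in the sample size cannot be squared with the Swedish mortality rates in the protocol's own Background

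*Protocol article*

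**What the plan says.** In the protocol article, Statistical analysis, the trial is planned to "reduce the primary outcome by one third from 2.74 to 1.84" %, with "level of significance 0.05, power 80 %, dropout rate 10" %. The 2.74 % is attributed to Region Skane, 2000–2010, at gestational week 41+3. It is built from HIE 0.22 %, MAS 0.36 %, brachial plexus injury 0.05 %, low five-minute Apgar score 1.58 %, and "stillbirth and neonatal mortality 0.53" %. The conclusion is: "We need a sample size of 10 038 women to be randomised". The primary test is Fisher's exact test, two-sided.

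Under Complications in postterm pregnancies, the same article states: "The PNM in Sweden between 2004 and 2013 was 0.3‰ in GW 39–41 and 0.7‰ after 42 GW". It defines perinatal mortality as stillbirth plus death within 7 days of birth. It also quotes stillbirth rates from 1982–1991. For weeks 41 and 42 these run from 0.50 to 2.27 per 1000, the highest being for first-time mothers at week 42 with foetuses at risk as the denominator.

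**The concern.** In common units, the planning input is 5.3 per 1000. The recent national figure nearest to the trial's setting is 0.7 per 1000, and no older Swedish rate quoted for weeks 41–42 exceeds 2.27 per 1000. The periods overlap (2000–2010 and 2004–2013), and the article does not mention the gap.

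Mortality supplies 0.53/2.74 = 19 % of the planned control rate. The effect is framed as a one-third relative reduction, so a lower control rate shrinks the absolute difference and lowers the power of a fixed sample. The stated 80 % therefore depends on an input that the article's own Background puts in doubt.

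**Working it through.** **Inputs.** From Statistical analysis: the five component rates, 2.74 % versus 1.84 %, significance level 0.05 and two-sided Fisher's exact test, 80 % power, 10 % dropout, 5 019 per arm. From Randomisation: 1:1 allocation. From the Background: the Swedish mortality rates above.

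**Step 1: reproduce the plan.**
- Sum of components: 0.22 + 0.36 + 0.05 + 1.58 + 0.53 = 2.74 %. Without mortality it is 2.21 %.
- Relative risk: 1.84/2.74 = 0.6715, a reduction of 32.8 %.
- Evaluable per arm after 10 % dropout: 5 019 × 0.90 = 4 517.
- Exact two-sided Fisher power at 2.74 % versus 1.84 % with 4 517 per arm: 80.1 %.
- As a cross-check, the continuity-corrected formula gives 4 555 per arm. Divided by 0.90 this is 5 062 per arm, 10 124 in total, within 1 % of the stated 10 038.

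The sample size follows from its inputs. The arithmetic is sound, and the question is about one input.

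**Step 2: size of the conflict.**
- Against 0.7 per 1000 (after 42 weeks): 0.53/0.07 = 7.6.
- Against 2.27 per 1000 (highest quoted stillbirth rate, weeks 41–42): 0.53/0.227 = 2.3.

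**Step 3: change this input only.** Control rate = 2.21 % + mortality; intervention rate = control rate × 0.6715; 4 517 per arm; exact Fisher power.

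| Mortality input | Source | Control | Intervention | Power |
|---|---|---|---|---|
| 0.53 % | as planned | 2.74 % | 1.84 % | 80.1 % |
| 0.227 % | highest quoted stillbirth rate | 2.44 % | 1.64 % | 74.9 % |
| 0.07 % | Sweden, after 42 weeks | 2.28 % | 1.53 % | 71.9 % |
| 0.053 % | if 0.53 was meant per mille (assumption) | 2.26 % | 1.52 % | 71.5 % |
| 0.03 % | Sweden, weeks 39–41 | 2.24 % | 1.50 % | 71.0 % |

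At a control rate of 2.28 %, the relative reduction detectable with 80 % power is about 36 %, against about 33 % as planned. Keeping 80 % power for the planned relative reduction would take about 12 200 women at 2.28 % by the continuity-corrected formula (5 495/0.90 per arm, 12 212 in total).

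**The case against.** **The comparators are not like for like.** The input is regional and at week 41+3, and the outcome counts neonatal deaths on days 0–27. The Background rate is national, from a partly different period, and counts deaths only to 7 days. The 2.27 per 1000 is stillbirth alone. All this stands, but the article gives nothing to show that these differences account for a 7.6-fold gap. A ratio of 18 can be formed against the 0.3 per 1000 figure, but that rate covers weeks 39–41, largely before the trial's window, and should not carry the point.

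**The Background rate may be the wrong one.** The article cites a meta-analysis with 469 inductions needed to prevent one perinatal death. That implies a difference of 1/469, about 2.1 per 1000, and so a mortality under expectant management of at least that much. This exceeds 0.7 per 1000, although the trials behind it are older and from other populations. The argument stands: the documents do not settle which figure is in error.

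**One input does not determine the power.** The primary outcome also includes metabolic acidosis, intracranial haemorrhage, convulsions and mechanical ventilation, none of which is in the 2.74 %. They would raise the rate, and 0.46 points from them would fully offset moving mortality to 0.07 %. Against that, the listed components are added as if no child had two of them, which overstates the rate. The net error cannot be found from the article. A reader might infer that the trial does not have 80 % power; the documents do not support so flat a statement.

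**The loss depends on conventions.** With all 5 019 per arm analysed, Fisher power is 76.5 % at 2.28 % and 79 % at 2.44 %. If the 0.9-point absolute difference were kept, power at 2.28 % would be about 89 % (normal approximation). However, the article plans for 10 % dropout and calls a 33 % relative reduction clinically relevant, so the calculation above follows its own terms.

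**Safety monitoring.** A reader might also infer that the monitoring board is working from a wrong expected number of deaths. The article states no such number, so that does not follow.

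**Conclusion.** The conflict is real and stands within one document: 5.3 per 1000 in the sample size against 0.7 per 1000 after 42 weeks in the Background, with no quoted stillbirth rate for weeks 41–42 above 2.27 per 1000. Which figure is wrong is open. A unit slip would fit, since 0.53 per mille lies between the two national rates, but nothing in the article confirms it.

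If 0.53 % is the wrong figure, this input alone takes the stated power from 80 % to between 71 % and 75 %, with about 72 % at the most relevant Background rate. That range assumes the planned relative reduction, 10 % dropout, Fisher's exact test and every other component rate unchanged. It measures sensitivity to one input and is not the trial's true power.

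**What to change.** 1. Check both mortality figures at source, including unit, denominator, gestational week and death window.
2. Correct the wrong figure. If both are right, add a sentence explaining why the planning rate is so much higher than the national one.
3. If 0.53 % falls, restate the composite control rate, the absolute difference and the power of 10 038 women.
4. Show power as a range over plausible control rates. State that 2.74 % leaves out four components of the primary outcome and ignores overlap between those it adds.

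The cost is a source check, a short recalculation and a few changed sentences. The design and analysis need no change for this. The stated power may become less favourable, in which case the sponsor would have to accept it or reconsider the sample size.

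### The primary test ignores the strata used for randomisation and is mildly conservative; a test stratified by centre and parity is a small, low-cost improvement

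*Protocol article*

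**What the plan says.** In the protocol article, *Randomisation* sets the allocation: "Block randomisation with a fix block size (unknown to the investigator) will be done online, 1:1". It adds: "Stratification will be performed for centre and parity (primiparity and multiparity". *Methods/Design* says the trial "will be performed at 4 university clinics and 1 county hospital in Sweden", so there are 5 × 2 = 10 strata.

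*Statistical analysis* makes the primary comparison of the composite a two-sided Fisher's "exact test on the intention to treat (ITT) [46] populations at significance level 0.05". No strata enter that test. On covariates it says: "Adjustments for baseline variables if necessary and interaction analyses will be performed with multivariable logistic regression analyses". It does not name the variables or say when adjustment becomes necessary. The statistician is to be blinded to group and intervention.

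The sample size assumes that early induction will "reduce the primary outcome by one third from 2.74 to 1.84" % ("level of significance 0.05, power 80 %, dropout rate 10" %), giving 5 019 women per arm and 10 038 in all.

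**The concern.** A trial that restricts randomisation within centre and parity would normally carry those factors into its primary analysis. If they predict the outcome, a test that ignores them tends to be conservative and a little less powerful. Fisher's test is also conservative in its own right when events are few. With a rare composite, even a small loss is worth avoiding if avoiding it costs nothing.

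The open-ended wording on adjustment is a secondary matter. It leaves the content of a supplementary model unsettled, although the obvious covariates are known before the first woman is randomised.

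**Working it through.** **Inputs.** From *Statistical analysis*: p₁ = 0.0274, p₂ = 0.0184, two-sided α = 0.05, power 80 %, dropout 10 %, 5 019 per arm. From *Randomisation* and *Methods/Design*: 1:1 allocation, 10 strata.

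**1. The plan's own sample size.** Analysed per arm: 5 019 × 0.9 = 4 517. Exact power is the sum, over all pairs of event counts that Fisher's test rejects, of Bin(x₁; n, p₁) × Bin(x₂; n, p₂). At n = 4 517 it is 80.07 %. Power first reaches 80 % at n = 4 509, which is 4 509/0.9 = 5 010 after dropout, within 9 women per arm of the stated figure. The sample size therefore fits the planned test.

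The uncorrected chi-square formula does not reproduce it:

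n = [1.960·√(2·0.0229·0.9771) + 0.842·√(0.0274·0.9726 + 0.0184·0.9816)]² / 0.009² ≈ 4 336 per arm.

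After dropout this is 4 336/0.9 → 4 818 per arm, or 9 636 in total, which is 10 038 − 9 636 = 402 fewer.

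**2. True size and power of the unstratified tests**, by the same enumeration with 4 517 per arm:

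| Quantity | Fisher | Uncorrected chi-square |
|---|---|---|
| Size, common rate 2.74 % | 4.31 % | 5.00 % |
| Size, common rate 2.29 % | 4.27 % | 4.99 % |
| Size, common rate 1.84 % | 4.18 % | 5.00 % |
| Power, 2.74 % vs 1.84 % | 80.07 % | 81.88 % |

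The chi-square test also ignores the strata, yet it holds 5 % and gains 81.88 − 80.07 = 1.8 points of power. That difference comes from discreteness alone.

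**3. What the strata add.** Simulation with 10 strata, arms balanced within each stratum and 100 000 replicates per scenario. The assumptions are half the women primiparous, centre shares of 28, 23, 30, 13 and 6 %, a primiparous-to-multiparous risk ratio of 1, 2 or 3, and a spread in centre log-risk of 0 or 0.5. The article gives no composite rates by centre or parity.

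| Parity ratio, centre spread | Size: Fisher / chi-square / CMH | Power: Fisher / chi-square / CMH |
|---|---|---|
| 1, 0 | 4.17 / 4.87 / 4.87 % | 79.88 / 81.71 / 81.71 % |
| 1, 0.5 | 4.27 / 4.91 / 4.93 % | 79.95 / 81.80 / 81.85 % |
| 2, 0 | 4.21 / 4.97 / 4.98 % | 80.23 / 82.05 / 82.08 % |
| 2, 0.5 | 4.34 / 5.04 / 5.12 % | 80.34 / 82.15 / 82.32 % |
| 3, 0 | 4.15 / 4.85 / 4.92 % | 80.04 / 81.82 / 82.02 % |
| 3, 0.5 | 4.16 / 4.80 / 4.92 % | 80.16 / 82.02 / 82.27 % |

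CMH is the Cochran-Mantel-Haenszel test without continuity correction. Its largest gain over the unstratified chi-square is 82.27 − 82.02 = 0.25 point of power and 4.92 − 4.80 = 0.12 point of size.

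**4. How sparse the strata are.** Expected events are 4 517 × (0.0274 + 0.0184) ≈ 207, about 21 per stratum on average. The smallest assumed centre (6 %) would have about 12 across its two parity strata.

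**The case against.** The strongest defence is that nothing here is wrong. An exact test that never exceeds 5 % is a reasonable choice for a 2 to 3 % outcome, the sample size fits it, and 2 points of power is close to a matter of taste. On validity and planned power this stands in full.

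It also disposes of several stronger readings that a reader might infer:

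- *Ignoring the strata is what pushes the size below 5 %.* It is not. The unstratified chi-square ignores them too and holds 5 %.
- *The trial is underpowered, or loses power it had bought.* It is not short of its target, because 10 038 fits Fisher's test. The 402 women are the price of choosing that test, already included in the design.
- *Parity is shown to be strongly prognostic for the primary outcome.* The figures in *Complications in postterm pregnancies* are for stillbirth only. At 42 weeks the primiparous-to-multiparous ratio is 2.26/0.86 = 2.6 per delivered woman but 2.27/1.51 = 1.5 per foetus at risk. In the sample-size paragraph, stillbirth and neonatal death make up 0.53 of the 2.74 percentage points. No parity ratio for the composite is given.
- *The adjustment clause lets the sponsor switch the primary result.* The article fixes one primary test with its sidedness, population and level. The clause concerns a supplementary analysis, and the statistician is blinded to group. When and how to adjust may also be set out in a fuller document that is not shown.

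What remains is narrower. The primary test is stated, not left open, and it does not follow the stratification that the same article prescribes. A test that does follow it costs no women and no data.

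**Conclusion.** The point holds as a minor one. The planned analysis is valid, does not inflate type I error and reaches its 80 % power. It is conservative, at about 4.2 to 4.3 % against 5 %, and a stratified Cochran-Mantel-Haenszel test would have about 82 % power at the same sample size. About 1.8 of those 2 points are due to Fisher's discreteness. Following the strata contributes at most about 0.3 point of power and 0.1 point of size.

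The Fisher and chi-square figures in the enumeration rest only on the article's event rates and 10 % dropout. The share attributed to the strata depends on the assumed centre sizes and spread and on parity ratios of 1 to 3. The case for stratifying is therefore mainly consistency between design and analysis, and the gain in power comes mostly from moving off Fisher's test.

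**What to change.** In *Statistical analysis*:

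1. Make the primary test a two-sided Cochran-Mantel-Haenszel test without continuity correction, stratified by centre and parity, with a rule set in advance for pooling small centres.
2. Report the common risk ratio or risk difference with its 95 % CI.
3. Keep Fisher's exact test as a named sensitivity analysis.
4. Replace the conditional wording on adjustment with the fixed set of centre and parity.

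This is a change of wording, to be made before unblinding, and the sample size can stay as it is. The cost is that the primary test becomes a large-sample test instead of an exact one, so its 5 % level is approximate (4.9 to 5.1 % in the scenarios above), and sparse strata may have to be pooled.
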